### Quality of Life

- **EORTC QLQ-C30**

Each domain will be summarised. The change from baseline will be summarized. For specific domains, a model based analysis will be undertaken (such as Mixed effects models). The scoring of the items/scales will be as described in the EORTC QOL Scoring Manual. Patients without a baseline assessment will be excluded from the analysis.

- **EORTC brain tumour module BN-20 questionnaire - Neurological symptoms (visual disorder, motor dysfunction, communication deficit, and drowsiness)**

Patients with recurrent glioblastoma commonly experience neurological symptoms. Therefore, improvement in visual disorders, motor dysfunction, communication deficits and drowsiness between the treatment arms for patients with neurological symptoms relative to baseline will be summarized by treatment group. Improvement in symptoms should also be concurrent with stable or decreasing use of steroids (dexamethasone). Visual disturbances will be assessed using questions 36, 37 and 38 of the BN-20. Motor dysfunction will be assessed using questions 40, 45, and 49 of the BN-20.

Communication deficits will be assessed using question 41, 42 and 43 of the BN-20. Drowsiness will be assessed by question 44.

## 16.5 Statistical Analysis of Safety Data

The following safety endpoints below will all be summarized using appropriate summary statistics. Changes from baseline may be conducted as is deemed appropriate. Safety data will be analysed and reported on an ongoing basis for IDMC meetings (where data is available).

- Adverse Events (AE)
- Vital signs including blood pressure (BP)
- Electrocardiogram (ECG) parameters
- Laboratory findings (clinical chemistry, haematology, urinalysis, TSH, T3 and T4)
- Physical examination including neurological examination

Safety data will be summarized as deemed appropriate. Relevant changes from baseline may be reported and summarized by treatment group. SAEs will be summarized by grade and treatment group. Safety data will be analysed and reported on an ongoing basis for IDMC meetings (where data is available).

### Stopping criteria

A treatment-related grade  $\geq 3$  toxicity rate of 30% in any treatment group along with any other clinical data agreed by the Independent data Monitoring Committee would be used as a guide to consider stopping the trial. As soon as 17 patients out of 56 (30%) in one of either arm suffer a grade  $\geq 3$  treatment-related event, this would prompt us to review the safety data more frequently. If at least 24 patients (43%) have a grade  $\geq 3$  treatment-related event, this would require the IDMC to consider stopping the trial early for safety reasons. The IDMC will be able to compare the toxicity rates between the treatment arms. All safety data will be reviewed regularly. This will be at least every 6 months by members of the TMG in a blinded fashion and at every IDMC meeting. Should stopping be considered due to safety reasons, the IDMC will meet at the earliest convenient time.

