### **12.5.3 Independent Data Monitoring Committee (IDMC)**

The role of the IDMC is to provide independent advice on data and safety aspects of the trial. Meetings of the Committee will be held regularly (yearly or based on any safety considerations or lack of efficacy considerations). The IDMC is advisory to the ITSC and can recommend premature closure of the trial to the ITSC. The IDMC charter will define the specific responsibilities of the IDMC.

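### The two numeric safety triggers match their stated rates only in a full arm of 56, so they act late, and 30% is given two different consequences

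*Protocol*

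**What the plan says.** The stopping criteria in protocol section 16.5 contain three statements about the rate of treatment-related events of grade 3 or higher.

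- The opening sentence takes a "toxicity rate of 30% in any treatment group along with any other clinical data agreed by the Independent data Monitoring Committee" and says that it "would be used as a guide to consider stopping the trial". It names no denominator.
- The second sentence sets a count: "As soon as 17 patients out of 56 (30%) in one of either arm suffer a grade" 3 or higher related event, "this would prompt us to review the safety data more frequently".
- The third sets a higher count: "If at least 24 patients (43%) have a grade" 3 or higher related event, the IDMC is required to consider stopping early. Its denominator is not written, but 43% corresponds to 56.

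On who looks and when, the same paragraph says of safety review: "This will be at least every 6 months by members of the TMG in a blinded fashion and at every IDMC meeting". It adds: "The IDMC will be able to compare the toxicity rates between the treatment arms". Section 12.5.3 says: "Meetings of the Committee will be held regularly (yearly or based on any safety considerations or lack of efficacy considerations"). If stopping is being considered on safety grounds, section 16.5 has the IDMC meet as soon as is convenient.

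**The concern.** A safety rule is needed most while patients are still being enrolled. A count that equals 30% or 43% of a complete arm is a much higher percentage of a partly filled one, so the numeric rule is least sensitive when acting on it would spare the most patients. The triggers also refer to a single arm, and the first takes effect the moment it is reached, whereas the six-monthly Trial Management Group review is blinded.

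Separately, an IDMC looking at, say, 35% in one arm cannot tell from the paragraph which consequence applies. By the first sentence that rate is a guide to consider stopping; by the second it calls only for more frequent review.

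**Working it through.** **Inputs.** Target of 112 patients and 18 months of accrual (section 16.1); 1:1 allocation (section 6.1), so 56 per arm; triggers of 17 and 24 (section 16.5). Assumptions: uniform accrual, equal arms, and each event counted at enrolment. The last is optimistic: time to onset, and CRF return of up to one month (section 9.5), delay the triggers further.

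**1. The plan's own percentages.** 17/56 = 30.4% and 24/56 = 42.9%. Both are reproduced, but only with the full arm as denominator.

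**2. What can occur without a trigger.** The most events that leave a trigger untouched are 16 and 23. As a share of the n patients treated in the arm:

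| n in arm | below the 17 trigger | below the 24 trigger |
|---|---|---|
| 16 | 16/16 = 100% | 16/16 = 100% |
| 23 | 16/23 = 70% | 23/23 = 100% |
| 28 | 16/28 = 57% | 23/28 = 82% |
| 37 | 16/37 = 43% | 23/37 = 62% |

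**3. Timing.** Accrual per arm is 56/18 = 3.11 patients a month, so about 19 at month 6 and 37 at month 12. The expected number treated when a trigger of r events is reached is r/p, at month (r/p)/3.11.

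| true rate p | 17 reached | 24 reached |
|---|---|---|
| 43% | patient 40, month 12.7 | patient 56, month 17.9 |
| 60% | patient 28, month 9.1 | patient 40, month 12.9 |
| 80% | patient 21, month 6.8 | patient 30, month 9.6 |

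**4. Probability of having triggered by month 12.** Exact binomial, P(X ≥ r) with n = 37.

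| true rate | P(X ≥ 17) | P(X ≥ 24) |
|---|---|---|
| 43% | 42% | 0.6% |
| 50% | 74% | 5% |
| 60% | 97% | 33% |

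At month 6 (n = 19) a count of 24 is impossible, and P(X ≥ 17) is 0.5% even at a true rate of 60%.

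**5. The same rates applied to patients treated so far.** Taking 24/56 as a running fraction gives thresholds of 9 of 20, 12 of 28 and 16 of 37. At a true 60% these are met with probability 94%, 98% and 99%. The price is false alarms: at a true 30% the threshold of 9 of 20 is met with probability 11%. An exact-binomial form, taking the smallest r with P(X ≥ r | 30%) ≤ 5%, needs 10 of 20, 13 of 28 or 17 of 37. At a true 60% it is met with probability 87%, 95% and 97%.

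**6. What pooled data can show.** A reviewer who sees only pooled counts can be sure that one arm has reached 17 only at 33 pooled patients (16 + 16 = 32 still allows neither), and 24 only at 47 (23 + 23 = 46).

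**The case against.** The strongest reply is that the counts are not the whole rule. The paragraph opens with a rate, and the IDMC can apply it at any stage because no denominator of 56 is attached. The IDMC sees rates by arm, may meet on any safety consideration, and must meet promptly once stopping is in question. At a month-12 meeting, 16 of 37 would be plainly above 30%, whatever the counts say. Serious events are also reviewed individually at the trials centre (section 10.2.2.5). All of this stands. A reader might infer that high toxicity would go unnoticed, or that the IDMC can act only once a year. The documents support neither.

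Nor does the first trigger stay silent for most of accrual: at a true 60% it is expected about half-way through and is 97% likely by month 12. The text does not call 30% or 43% unacceptable; both are prompts for judgement.

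Who keeps the per-arm count between meetings may be settled in the IDMC charter, which section 12.5.3 says will define the committee's responsibilities and which is not at hand. It would therefore be wrong to conclude that nobody does so.

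Fixed counts also have a merit: they seldom raise a false alarm. With looks every three patients from 20 onwards, a bare running rate at a true 25% crosses the 30% line at some look 46% of the time, against 22% for the count of 17. At a true 30% it crosses the 43% line 18% of the time, against 2.8% for the count of 24. This argues against a bare running proportion, but not for having no threshold before 56.

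Finally, the two uses of 30% could be read as graded escalation. That is possible, but the wording does not say so.

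**Conclusion.** The point holds as one of late action and unclear wording. Both numeric triggers correspond to their stated rates only in a complete arm, and the protocol gives no threshold for fewer patients. With about 37 per arm at month 12, the count that obliges the IDMC to consider stopping has been reached with probability 0.6%, 5% and 33% at true rates of 43%, 50% and 60%. The count for closer review does better, at 42%, 74% and 97%. The opening 30% guide and the IDMC's freedom to meet soften the consequence, but they leave the numeric rule unable to respond early and they leave 30% with two meanings.

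The percentages by number treated need no assumption. The month-12 figures rest on uniform accrual, equal arms and no reporting lag; any lag makes the triggers later. This should be fixed, because it is a safety rule that the protocol itself states and the correction is cheap.

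**What to change.** - Restate the existing rates as proportions of patients treated to date in each arm, from a stated minimum number. Use an exact-binomial or lower-confidence-limit criterion, set out as a short table of counts by number treated. The counts of 10 of 20, 13 of 28 and 17 of 37 illustrate the form for a reference rate of 30%. Because the 5% applies at each look, the table should be calibrated for the planned number of looks.
- Supply that per-arm tabulation to the IDMC between meetings, through the route by which it already receives safety data by arm. The Trial Management Group can then stay blinded.
- Reconcile the opening sentence with the two that follow, so that one consequence attaches to 30% and one to 43%. The choice of rates and consequences belongs to the sponsor and the IDMC.

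The cost is a wording change in section 16.5 and the IDMC charter, plus a brief periodic table from data already due within a month of each visit. The drawback is some extra false alarms at small numbers, limited by the minimum number and the exact criterion.

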## 16.6 Statistical Analysis of other endpoints

### Pharmacodynamic and Pharmacogenetic endpoints

- Levels of soluble markers of angiogenesis and tumour growth including changes from baseline using optional blood samples
- Biomarker analysis from archival and postmortem tumour samples
- Pharmacogenetic analysis using optional blood samples and/or tumour samples

Blood samples (plasma and serum) will be collected and assessed for biomarkers of disease activity, effect of cediranib and gefitinib, and angiogenesis. Archival tumour samples (from the primary tumour and/or any recurrent disease) will be collected from patients who provide informed consent for the retrospective analysis of biomarkers. Biomarkers will be investigated for possible correlation with key clinical outcomes and for the effects of the study medication.

Appropriate summaries of absolute levels and changes from baseline in soluble biomarkers will be produced, as well as correlates with clinical efficacy. Summaries of biomarkers in archival tumour samples and appropriate correlates will be produced. Additional analysis may be conducted as deemed appropriate.

## 16.7 Handling missing data

Missing data will be left as missing and no imputation will be carried out. Further details where relevant will be outlined in the SAP.

## 16.8 Interim Analysis

No formal interim analysis is planned. However data is reviewed on an ongoing basis for the IDMC. In addition, conditional power estimates may be provided to determine futility of the trial based on the observed and assumed hazard ratio. This will be calculated at 50% of the required events and 75% of the events stated in the sample size section. In general a conditional power of < 20% is suggestive of futility, however clinical judgment will also be taken into account before concluding formal futility of the trial.

---

## 17.0 Ethical and Regulatory Approvals

In conducting the Trial the Sponsor, UCL CTC and Sites shall also comply with all laws and statutes, as amended from time to time, applicable to the performance of clinical trials including, but not limited to:

- the principles of ICH Harmonised Tripartite Guideline for Good Clinical Practice (CPMP/ICH/135/95) as set out in Schedule 1 (Conditions and Principles of Good Clinical Practice and for the Protection of Clinical Trial Subjects) of the Medicines for Human Use (Clinical Trials) Regulations 2004 and the GCP Directive 2005/28/EC, as set out in SI 2006/1928
- the Human Rights Act 1998
- the Data Protection Act 1998
- the Freedom of Information Act 2000
- the Human Tissue Act 2004
- the Medicines Act 1968
- the Medicines for Human Use (Clinical Trials) UK Regulations SI 2004/1031, and subsequent amendments
- Good Manufacturing Practice
- the Research Governance Framework for Health and Social Care, issued by the UK Department of Health (Second Edition 2005) or the Scottish Health Department Research Governance Framework for Health and Community Care (Second Edition 2006)

### 17.1 Ethical Approval

The trial will be conducted in accordance with the World Medical Association Declaration of Helsinki entitled 'Ethical Principles for Medical Research Involving Human Subjects' (1996 version) and in accordance with the terms and conditions of the ethical approval given to the trial.

The trial has received a favourable opinion from the [REC name to be inserted when favourable opinion granted] Research Ethics Committee.

UCL CTC will submit Annual Progress Reports to the REC, which will commence one year from the date of ethical approval for the trial.

## 17.2 Regulatory Approval

A Clinical Trial Authorisation (CTA) has been granted for the trial.

The trial will be conducted at approved trial sites in accordance with the trial protocol and the terms of the CTA granted by the MHRA.

## 17.3 Local Site Approval

The Lead Comprehensive Local Research Network (CLRN) has given NHS permission following global governance checks. Local checks will be undertaken by local CLRNs associated with individual trial sites.

Evidence of local Trust R&D approval must be provided to UCL CTC prior to site activation. The trial will only be conducted at sites where all necessary approvals for the trial have been obtained.

## 17.4 Protocol Amendments

UCL CTC will be responsible for gaining ethical and regulatory approvals for all amendments made to the protocol and other trial-related documents. Once approved, UCL CTC will ensure that all amended documents are distributed to sites and CLRNs as appropriate.

Site staff will be responsible for acknowledging receipt of documents and for gaining local Trust R&D acknowledgement for all amendments and approval for substantial amendments, and for providing UCL CTC with evidence of this.

## 17.5 Patient Confidentiality & Data Protection

Patient identifiable data, including initials, date of birth, and NHS number will be required for the randomisation process and will be provided to UCL CTC. UCL CTC will preserve patient confidentiality and will not disclose or reproduce any information by which patients could be identified. Data will be stored in a secure manner and UCL CTC trials are registered in accordance with the Data Protection Act 1998 with the Data Protection Officer at UCL.

---

### 18.2 Indemnity

University College London holds insurance to cover participants for injury caused by their participation in the clinical trial. Participants may be able to claim compensation if they can prove that UCL has been negligent. However, as this trial is being carried out in a hospital, the hospital continues to have a duty of care to the participant of the trial. University College London does not accept liability for any breach in the hospital's duty of care, or any negligence on the part of hospital employees. This applies whether the hospital is an NHS Trust or not. This does not affect the participant's right to seek compensation via the non-negligence route.

Participants may also be able to claim compensation for injury caused by participation in this trial without the need to prove negligence on the part of University College London or another party. Participants who sustain injury and wish to make a claim for compensation should do so in writing in the first instance to the Chief Investigator, who will pass the claim to the Sponsor's Insurers, via the Sponsor's office.

Hospitals selected to participate in this trial shall provide clinical negligence insurance cover for harm caused by their employees and a copy of the relevant insurance policy or summary shall be provided to University College London, upon request.

## 19.0 Funding

Cancer Research UK and AstraZeneca are supporting the central coordination of the trial through the UCL CTC. AstraZeneca will be providing the cediranib, gefitinib and placebo free of charge.

## 20.0 Publication Policy

All publications and presentations relating to the trial will be authorised by the Trial Management Group (TMG). The first publication of the trial results will be written by and in the name of the TMG, relevant trial staff from UCL CTC, and the Trial statistician. Authors will be cited by name if published in a journal where this does not conflict with the journal's policy. Contributing site Investigators (PIs plus Co-Investigators and research nurses where appropriate) will be acknowledged, along with AstraZeneca and the trial participants (anonymously). Data from all sites will be analysed together and published as soon as possible. Participating sites may not publish trial results prior to the first publication by the TMG or without prior written consent from the TMG. The trial data are owned by UCL the sponsor. However, AstraZeneca will be permitted to see the draft manuscripts and make comments at least 30 days prior to submission for publication. The Clinicaltrials.gov number allocated to this trial will be quoted in any publications based upon its results.

## 21.0 Translational Research

An exploratory translational part of the research will look at blood, tumour and post-mortem samples for which additional and optional consent will be obtained from patients.

The objectives of the translational research are:

- To investigate the relationship between the effects of cediranib on soluble angiogenesis biomarkers and clinical efficacy
- To obtain blood samples for pharmacogenetics (genetic variation giving rise to different response to the IMPs)
- To obtain archival tumour biopsy samples for biomarker analysis and potential sub-group stratification for:
  - IDH1 and 2 (Yan et al. 2009)
  - MGMT methylation status
  - EGFR, EGFRvIII and PTEN (Mellinghoff et al. 2005)
- To obtain post-mortem tumour samples for research into genomic sequence and/or gene expression patterns associated with response or resistance to cediranib and/or gefitinib.

As consent for this part of the research is optional, it is not known whether sufficient data will be generated to explore all of the above objectives. Patients will consent to donate samples for future research, consent will be generic and enduring and include consent for genetic research. Consent for blood and tumour samples will be separate from post-mortem samples.

Blood samples will be taken at time-points outlined in the schedule of assessments ([section 8.1](#)). Staff members taking samples should be appropriately qualified to do so. These will include serum samples and whole blood samples in EDTA. Samples will be stored locally at sites in freezers and collected in batches (remaining frozen) for storage at the laboratory in UCL.

Archival tumour biopsies will be collected from patients where they have given consent for this. Post mortem tumour samples will be collected where patients have given additional consent for this. These samples will be collected and stored at the laboratory in UCL.

Sample collection, storage and shipping arrangements will be described in a separate Laboratory Manual. Sample labels will refer to patient trial number, but not to patient names.

Translational research will be retrospective to the trial. Translational research will be in line with the current evolving literature at the end of the trial and available resources and where possible will also include the following: EGFR mutation analysis, amplification of 4q (VEGFR2, PDGFR, c-Kit), and VEGF/VEGFR polymorphisms. Where possible, DNA and/or RNA will be extracted from blood and tumour samples and analysed using methods such as whole-genome sequencing, microarray analysis and gene methylation profiling. Any additional objectives for the translational research will be submitted for additional ethics approval.

Extraction of post-mortem samples will be carried out by local pathologists and will only be available at sites where this has been agreed in the clinical trial site agreement. Families of patients who have consented to donation of post-mortem samples will need to contact the local investigator at the site to arrange this. Post-mortem tissue samples taken will be of the tumour and brain only.

| SAMPLE                                | Baseline                         | Week 6          | Week 12         | Week 18         | Week 24         | Discontinuation | Death                               |
|---------------------------------------|----------------------------------|-----------------|-----------------|-----------------|-----------------|-----------------|-------------------------------------|
| Pharmacodynamic (serum)        | 10ml (drawn)                     | 10ml (drawn)    | 10ml (drawn)    | 10ml (drawn)    | 10ml (drawn)    | 10ml (drawn)    |                                     |
| Pharmacodynamic (whole blood)  | 10-20ml in EDTA                  | 10-20ml in EDTA | 10-20ml in EDTA | 10-20ml in EDTA | 10-20ml in EDTA | 10-20ml in EDTA |                                     |
| Pharmacogenetics (whole blood) | 10-20ml in EDTA                  |                 |                 |                 |                 |                 |                                     |
| Archival tumour sample         | Collected at end or during trial |                 |                 |                 |                 |                 |                                     |
| Post-mortem tumour sample      |                                  |                 |                 |                 |                 |                 | Collected after contact from family |

**Table 12** *Samples proposed for collection for translational research*

If there might be any problems with sample collection at the site, the DORIC trial coordinator should be contacted prior to site activation.

